#### 4.4.6. QTc

For the corrected QT (QTc) analyses, no values will be imputed for missing data.

#### 4.5. Statistical Considerations of COVID-19 Impacted Data

In March 2020, the World Health Organization (WHO) announced a global pandemic of the virus SARS-CoV-2 and the resulting disease COVID-19. During the conduct of this trial, if any participant's data is impacted by this pandemic, the following considerations will be given in the data analyses:

- a. If a participant dropped out of the study during the DLT evaluation window in Parts 1A, 1B, [REDACTED] due to COVID-19 and does not meet the DLT evaluation criteria, a replacement participant may be added.
- b. Death caused by COVID-19 is still considered as an "event" in the analysis of PFS and OS. If deemed necessary, a sensitivity analysis may be performed where COVID-19 driven death is censored at the death date.
- c. If a scheduled tumor radiographic scan is *delayed* out of the Schedule of Activity allowable window, or is *missing* (ie, participant skipped a scheduled tumor radiographic scan) due to any reasons related to the pandemic, this delay or missingness does not alter the censoring rules for PFS or TTP. A censoring reason of "COVID-19" may be added to the PFS or TTP summary if the specific reason of

[REDACTED]

PFIZER CONFIDENTIAL

Page 23

[REDACTED]

tumor scan delay or missing can be attributed to COVID-19. If deemed necessary, a sensitivity analysis may be performed where participants would be censored on the date of COVID-19 diagnosis.

- d. Any COVID-19 related symptoms are to be captured as adverse events in the case report form. Those adverse events will be summarized in the same manner as other adverse events. If a label or phrase of COVID-19 can be identified in the investigator provided adverse event term, then a separate AE listing may be provided for just the COVID-19 related events.
- e. If identifiable, the COVID-19 related data points, including missing data where the reason of missing is identified as COVID-19 related (site closure hence data could not be captured; participants skipped a visit because of concern over the pandemic), protocol deviations driven by COVID-19, safety events caused by COVID-19 may be separately listed.

## 5. ANALYSES AND SUMMARIES

### 5.1. Primary Endpoint(s)

#### 5.1.1. Dose-Limiting Toxicities (DLTs)

The DLT events will be summarized by dose level. A listing of the DLTs events will also be provided in which the participant primary diagnosis (malignancy), dose level the participant was enrolled to, DLT event start day and stop day relative to the cycle 1 day 1 dose date, the DLT event term, NCI CTCAE grade, relatedness to the investigational product (PF-07248144), or Fulvestrant (Part 1B), [REDACTED] outcome of the event, along with other variables deemed important, will be included.

### 5.2. Safety Endpoint(s)

*All safety analyses will be performed on the safety population.*

*Summaries and analyses of safety parameters will include all participants in the safety analysis set.*

*AEs, ECGs, BP, pulse rate, continuous cardiac monitoring, and safety laboratory data will be reviewed and summarized on an ongoing basis during the study to evaluate the safety of participants. Any clinical laboratory, ECG, BP, and PR abnormalities of potential clinical concern will be described. Safety data will be presented in tabular and/or graphical format and summarized descriptively, where appropriate.*

*Medical history and physical examination and neurological examination information, as applicable, collected during the course of the study will be considered source data and will not be required to be reported, unless otherwise noted. However, any untoward findings identified on physical and/or neurological examinations conducted during the active collection period will be captured as AEs, if those findings meet the definition of an AE.*

*Data collected at screening that are used for inclusion/exclusion criteria, such as laboratory data, ECGs, and vital signs, will be considered source data, and will not be required to be reported, unless otherwise noted. Demographic data collected at screening will be reported.*

### 5.2.1. Adverse Events

*AEs will be graded by the investigator according to the CTCAE version 5.0 and coded using MedDRA. AE data will be reported in tables and listings. Summaries of adverse event by mapped terms, appropriate thesaurus level, toxicity grade, and seriousness and relationship to study treatment will be presented, as well as summaries of adverse events leading to death and premature withdrawal from study treatment. The number and percentage of participants who experienced any AE, SAE, treatment related AE, and treatment related SAE will be summarized according to worst toxicity grades. The summaries will present AEs on the entire study period. Listings of DLTs and deaths will be provided.*

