### **8.3.1. Time Period and Frequency for Collecting AE and SAE Information**

The time period for actively eliciting and collecting AEs and SAEs (“active collection period”) for each participant begins from the time the participant provides informed consent, which is obtained before the participant’s participation in the study (ie, before undergoing any study-related procedure and/or receiving study intervention), through and including a minimum of 28 calendar days, except as indicated below, after the last administration of the study intervention.

During the long-term follow-up period in this study for survival, only SAEs will be actively elicited and collected after completion of the active collection period described above. The SAEs identified during long-term follow-up will be reported to Pfizer Safety on the CT SAE Report Form only if considered reasonably related to the study intervention.

Follow-up by the investigator continues throughout and after the active collection period and until the AE or SAE or its sequelae resolve or stabilize at a level acceptable to the investigator and Pfizer concurs with that assessment.

For participants who are screen failures, the active collection period ends when screen failure status is determined.

If the participant withdraws from the study and also withdraws consent for the collection of future information, the active collection period ends when consent is withdrawn.

If a participant definitively discontinues or temporarily discontinues study intervention because of an AE or SAE, the AE or SAE must be recorded on the CRF and the SAE reported using the CT SAE Report Form.

Investigators are not obligated to actively seek AEs or SAEs after the participant has concluded study participation. However, if the investigator learns of any SAE, including a death, at any time after a participant has completed the study, and he/she considers the event to be reasonably related to the study intervention, the investigator must promptly report the SAE to Pfizer using the CT SAE Report Form.

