#### **8.3.1.2. Recording Nonserious AEs and SAEs on the CRF**

All nonserious AEs and SAEs occurring in a participant during the active collection period, which begins after obtaining informed consent as described in [Section 8.3.1](#) will be recorded on the AE section of the CRF.

The investigator is to record on the CRF all directly observed and all spontaneously reported AEs and SAEs reported by the participant.

If a participant begins a new anticancer therapy, the recording period for nonserious AEs ends at the time the new treatment is started; however, SAEs must continue to be recorded on the CRF during the above-indicated active collection period. Note that a switch to a commercially available version of the study intervention is considered as a new anticancer therapy for the purposes of SAE reporting.

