#### **9.4.5.2. Adverse Events**

AEs will be graded by the investigator according to the CTCAE version 5.0 and coded using MedDRA. AE data will be reported in tables and listings. Summaries of adverse event by mapped terms, appropriate thesaurus level, toxicity grade, and seriousness and relationship to study treatment will be presented, as well as summaries of adverse events leading to death and premature withdrawal from study treatment. The number and percentage of participants who experienced any AE, SAE, treatment related AE, and treatment related SAE will be summarized according to worst toxicity grades. The summaries will present AEs both on the entire study period and by cycle (Cycle 1 and Cycles beyond 1). Listings of DLTs and deaths will be provided.

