## **2.4. Safety Endpoints**

For safety summaries, unless other specified, safety data are summarized for the data collected during “on-treatment period”, which is defined as the period that starts with the first dose date and ends at min(last dose date + 28 days, start of new anti-cancer therapy – 1 day). Anti-cancer radiation or surgery is not considered as a start of new anti-cancer therapy.

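### SAP 5.2.1 and 5.2.2 leave the period of the primary AE and laboratory summaries undefined, and drop the by-cycle summaries that the protocol still requires

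*Protocol*

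**What the plan says.** AEs and laboratory abnormalities, each characterised partly by their timing, are primary endpoints in Part 1 and Part 2 (SAP 2.1.1 and 2.1.2; protocol section 3).

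The general rule is in SAP 2.4: "For safety summaries, unless other specified, safety data are summarized for the data collected during" an on-treatment period. That is "the period that starts with the first dose date and ends at min(last dose date + 28 days, start of new anti-cancer therapy", less one day.

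The analysis sections do not repeat that window uniformly:

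- SAP 5.2.1 (AEs): "The summaries will present AEs on the entire study period".
- SAP 5.2.2 (laboratory tests): similar whole-study wording.
- SAP 5.2.3 (vital signs): names the on-treatment period explicitly.

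The protocol's counterpart for AEs, section 9.4.5.2, is fuller: "The summaries will present AEs both on the entire study period and by cycle (Cycle 1 and Cycles beyond 1"). Section 9.4.5.3 makes the same pair of commitments for laboratory tests.

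On data collection, protocol 8.3.1 says that the active period "for each participant begins from the time the participant provides informed consent". Protocol 8.3.1.2 ends the recording of nonserious AEs when new anticancer therapy starts, but "SAEs must continue to be recorded on the CRF during the above-indicated active collection period". In survival follow-up, "only SAEs will be actively elicited and collected after completion of the active collection period".

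**The concern.** The tables of a primary endpoint need a stated window. Here one section sets a default that yields to anything specified elsewhere, and another uses a different, undefined term. Two programmers could follow the SAP faithfully and produce different AE tables. Because collection starts at consent, one version could count events that precede any drug, including complications of the fresh biopsy that is mandatory when archival tissue is missing or insufficient.

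Separately, the SAP repeats the protocol's sentence without its second half. The Cycle 1 versus later-cycle split is the only tabulation of AEs by time that either document names, and timing is part of the endpoint.

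**Working it through.** The plan states no figure to reproduce, so the check compares the texts, counts days and takes one bound from the protocol's data.

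**1. Windows side by side**

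| Section | Data | Period | By cycle? |
|---|---|---|---|
| Protocol 9.4.5.2 | AEs | whole study, undefined | yes |
| Protocol 9.4.5.3 | laboratory | whole study, undefined | yes |
| SAP 2.4 | safety default | first dose to min(last dose + 28 days, new therapy - 1 day) | not addressed |
| SAP 5.2.1 | AEs | whole study, undefined | no |
| SAP 5.2.2 | laboratory | whole study, undefined | no |
| SAP 5.2.3 | vital signs | on-treatment, named | not addressed |

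**2. The two readings of SAP 5.2.1**

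- *Reading A: all cycles together, inside the SAP 2.4 window.* Pre-dose events are out. SAEs after new anti-cancer therapy are also out.
- *Reading B: an exception that SAP 2.4 allows, covering everything collected.* Pre-dose events are in. SAEs after new therapy are also in.

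The protocol's sentence favours A. The whole period is contrasted with two cycle strata, and a pre-dose event belongs to neither stratum, so the strata would not add up to the total under B. The SAP deletes that contrast, and SAP 5.2.3 shows that the authors name the on-treatment period when they mean it. Both facts make B easier to defend. The text does not settle the matter.

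**3. Days at issue**

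- Before dosing: screening is up to 28 days before Cycle 1 Day 1, so up to 28 days of collection differ between A and B.
- Food-effect subset: the first dose is on Cycle 1 Day -7. If Cycle 1 Day 1 were programmed as the start, Days -7 to -1 (7 days) would wrongly be treated as pre-dose. SAP section 3 already counts this dose for the safety analysis set.
- After the last dose (day L): if new therapy starts on day L + k, with k from 1 to 28, the SAP 2.4 window closes on L + k - 1. SAEs on days L + k to L + 28 are recorded but fall outside it. That is 28 - k + 1 = 29 - k days: 28 days for k = 1, 19 for k = 10, 1 for k = 28. The values of k are illustrative; the documents do not give the timing of later therapy.

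**4. Room for the headline figure to move**

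Protocol 2.2.4 reports a treatment-related AE in 52 of 59 participants (88.1%). In that data cut, pre-dose events could therefore have raised the proportion with any AE by at most (59 - 52)/59 = 7/59 = 11.9 percentage points. Any larger effect would have to be in counts by term, grade or seriousness.

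**5. The dropped split**

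SAP section 1 lets the SAP depart from the protocol, but says that major changes to the primary endpoint's definition or analysis will also appear in a protocol amendment. SAP version 2 (22 May 2023) is tied to Amendment 4 (14 November 2022), which still contains the by-cycle summaries. The two documents therefore disagree on what will be tabulated.

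**The case against.** The strongest reply is that SAP 2.4 already supplies a treatment-emergent rule for all safety summaries, and that the whole-study phrase in SAP 5.2.1 is only the remnant of a contrast with by-cycle tables. On that view nothing pre-dose enters. This is a good reading and may be the intended one. What remains is that the SAP does not say so, and its exception clause leaves the other reading open.

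Other points on that side stand:

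- Dose finding is not affected. MTD determination uses DLTs in the per-protocol set, over 28 days plus the Cycle 2 Day 1 laboratory tests (protocol 4.3.5 and 9.4.1).
- Treatment-related tables are separate and should not gain events that precede any drug.
- For laboratory data, SAP 5.2 treats screening values used for eligibility as source data that need not be reported, so the pre-dose problem is weaker there than for AEs.
- Closing the window at new anti-cancer therapy is defensible. Recording of nonserious AEs stops then, so keeping later SAEs in an all-AE table would mix two observation periods. Protocol 8.3.1.2 requires those SAEs to be recorded, not tabulated with the rest.
- The SAP may modify descriptive plans. Whether dropping the split is a major change is arguable; that it contradicts the current protocol is not.

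A reader might go further and infer that the study period starts at consent, that no treatment-emergent rule exists, or that pre-dose events are counted while late SAEs are dropped. The documents do not support this. Consent starts the collection period; no section makes it the start of the analysis period. SAP 2.4 is a first-dose rule. The two consequences belong to alternative readings, so they cannot both apply to one table.

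**Conclusion.** The point holds as an ambiguity and an omission, not as a proven contradiction over pre-dose events. The period for the primary AE and laboratory summaries is undefined in SAP 5.2.1 and 5.2.2 and can be read as overriding SAP 2.4. The by-cycle summaries promised in protocol 9.4.5.2 and 9.4.5.3 are missing from the SAP, whichever reading is taken.

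In time, the size is up to 28 pre-dose days per participant. The number of events cannot be stated, because the documents give no pre-dose AE rate and any percentage would be an assumption. The 11.9-point ceiling rests on one data cut of 59 participants and assumes that treatment-related AEs follow dosing. The change is worth making because these are primary-endpoint tables and it is cheap; it bears on descriptive safety reporting only.

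**What to change.** - In SAP 5.2.1 and 5.2.2, and in protocol 9.4.5.2 and 9.4.5.3, state that the summaries cover the on-treatment period of SAP 2.4, starting at the first dose of study intervention, including Cycle 1 Day -7 in the food-effect subset.
- List AEs with onset before first dose separately.
- List SAEs recorded after the start of new anti-cancer therapy separately, and keep them out of the all-AE tables.
- Restore the Cycle 1 and later-cycle summaries for AEs and laboratory tests in the SAP, and say that Day -7 to Day -1 in the food-effect subset counts with Cycle 1.

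The cost is wording in four sections, a window flag and a cycle flag in programming, and a few more tables and listings. No new data are needed: onset dates and dosing dates are already collected, and SAP 5.7.3 already defines Day 1 of each cycle.

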### 5.2.2. Laboratory Test Abnormalities

*The number and percentage of participants who experienced laboratory test abnormalities will be summarized according to worst toxicity grade observed for each laboratory assay. The analyses will summarize laboratory tests on the entire study. For laboratory tests without CTCAE grade definitions, results will be categorized as high, normal, or low. .*

### 5.2.3. Vital Sign Abnormalities

*Vital signs including temperature, pulse rate, respiratory rate, and blood pressure, will be assessed.*

*The vital signs will be generally considered as continuous endpoints. However the summaries of vital signs as continuous variables will not be provided as they may not be clinically meaningful. Instead, vital signs during the on-treatment period will be summarized by the categories of abnormality as specified in [Appendix 1](#). Shift tables will not be provided unless deemed necessary.*

### 5.2.4. Electrocardiogram Parameters

*Changes from baseline for the following ECG parameters: QT interval, heart rate, QTc interval, PR interval, and QRS complex will be summarized by treatment and time.*

*The number (%) of participants with maximum postdose QTc values and maximum increases from baseline in the following categories will be tabulated by treatment:*

#### Safety QTc Assessment

| Degree of Prolongation | Mild (msec) | Moderate (msec) | Severe (msec) |
|------------------------|-------------|-----------------|---------------|
| Absolute value         | >450-480    | >480-500        | >500          |
| Increase from baseline |             | 30-60           | >60           |

*In addition, the number of participants with uncorrected QT values >500 msec will be summarized.*

*If more than 1 ECG is collected at a nominal time after dose administration (for example, triplicate ECGs), the mean of the replicate measurements will be used to represent a single observation at that time point. If any of the 3 individual ECG tracings has a QTc value > 500 msec, but the mean of the triplicates is not > 500 msec, the data from the participant's individual tracing will be described in a safety section of the CSR in order to place the > 500-msec value in appropriate clinical context. However, values from individual tracings within triplicate measurements that are > 500 msec will not be included in the categorical analysis unless the average from the triplicate measurements is also > 500 msec. Changes from baseline will be defined as the change between the postdose QTc value and the average of the time-matched baseline triplicate values on Day -1, or the average of the predose triplicate values on Day 1.*

*In addition, an attempt will be made to explore and characterize the relationship between plasma concentration and QT interval length using a PK/PD modeling approach. If a PK/PD relationship is found, the impact of participant factors (covariates) on the relationship will be examined.*

*The analysis of ECG results will be based on participants in the safety analysis set with baseline and on-treatment ECG data. Baseline is defined as Cycle 1 Day 1 predose.*

*ECG measurements (an average of the triplicate measurements) will be used for the statistical analysis and all data presentations. Any data obtained from ECGs repeated for safety reasons after the nominal time-points will not be averaged along with the preceding triplicates. Interval measurements from repeated ECGs will be included in the outlier analysis (categorical analysis) as individual values obtained at unscheduled time points.*

*QT intervals will be corrected for HR (QTc) using standard correction factors (ie, Fridericia's [default correction], Bazett's, and possibly a study-specific factor, as appropriate). Data will be summarized and listed for QT, HR, RR, PR, QRS, QTcF (and other correction factors, eg, QTcB as appropriate), and by dose level in Part 1A and by group in Part 2 (Part 2A and Part 2B). Individual QT (all evaluated corrections) intervals will be listed by dose and time in Part 1A and by cohort and time in Part 2. The most appropriate correction factor will be selected and used for the following analyses of central tendency and outliers and used for the study conclusions. Descriptive statistics (n, mean, median, standard deviation, minimum, and maximum) will be used to summarize the absolute corrected QT interval and changes from baseline in corrected QT after treatment by study cohort, dose and time point.*

### 5.3. Secondary Endpoint(s)

#### 5.3.1. Pharmacokinetic Parameters

##### 5.3.1.1. Single Dose and Steady-State PF-07248144 Pharmacokinetic Analysis (With the Exception of Food Effect Assessment) [REDACTED]

##### 5.3.1.2.

*Following single dose administration, plasma PK parameters* [REDACTED]

*will be estimated.*

090177e19dab896e\Approved\Approved On: 07-Jun-2023 12:23 (GMT)

[REDACTED]

[REDACTED]

[REDACTED]

[REDACTED]

[REDACTED]

[REDACTED]

[REDACTED]

#### **5.3.1.3. Effect of Food on PF-07248144 Pharmacokinetics (Part 2A)**

[REDACTED]

[REDACTED]

[REDACTED]

#### **5.3.1.5. Pharmacodynamic and Biomarker Analyses**

*Results from PD and biomarker exploratory analyses will be reported in the CSR where possible. However, given the exploratory nature of exploratory objectives and endpoints, the*

[REDACTED]

PFIZER CONFIDENTIAL

Page 28

[REDACTED]

*analyses may not be complete at the time of the CSR. Results from exploratory analyses that are not included in the CSR will be shared with the scientific community through publication at a scientific conference and/or in a peer-reviewed scientific journal.*

### 5.3.2. Population Pharmacokinetic Analysis [REDACTED]

Results from PD and biomarker exploratory analyses will be reported in the CSR where possible. However, given the exploratory nature of exploratory objectives and endpoints, the analyses may not be complete at the time of the CSR. Results from exploratory analyses that are not included in the CSR will be shared with the scientific community through publication at a scientific conference and/or in a peer-reviewed scientific journal.

### 5.4. Efficacy Endpoint(s)

BOR, DOR, CBR, and PFS as assessed by investigator based on RECIST v1.1, are exploratory endpoints in Part 1 to evaluate the anti-tumor activity of PF-07248144. They, along with TTP, as assessed by investigator based on RECIST version 1.1, and Overall Survival are secondary endpoints in Part 2.

*Full Analysis Set will be used for all response related analyses including BOR, PFS, TTP, and OS. DOR will be analyzed only on responders.*

*Tumor response will be presented in the form of participant data listings that include, but are not limited to tumor type, dose on Day 1, tumor response at each visit, and best overall response. Proportion of participants responding to the treatment will be presented for each dose level.*

*For prostate cancer only, PSA and bone scan monitor, report and analysis should follow PCWG3 guidelines (see Protocol) Existing or new bone lesions as assessed by radionuclide bone scan will be described and documented.*

*PSA data will be presented in form of listings that include dose on Day 1, measurement, and % change from baseline at visit.*

*Part 1A, Part 1B, [REDACTED] Progression date, date of first response, last tumor assessment date, and date of last contact will be listed.*

*Part 2: The Kaplan-Meier method will be used to analyze all time to event endpoints. Median PFS (if reached) will be calculated. DOR will be listed. Efficacy data of participants from Part 1A, Part 1B, [REDACTED] treated at the dose level selected for the corresponding expansion cohort and satisfying inclusion/exclusion criteria might be included in the analysis of efficacy endpoints of Part 2.*

Part 1 and Part 2 data will be summarized separately, and may also be pooled together for analysis if deemed necessary, eg, to account for food effects subgroups. Specifically, the key tables in Part 2 include:

1. BOR is the best response recorded from the randomization until disease progression or death due to any cause. This is derived from the sequence of objective statuses. Objective statuses are not considered after objective progression is documented or after start of the first anticancer treatment post discontinuation of protocol treatment. BOR for each patient will be derived as one of the following categories.
  - Complete Response (CR): Two objective statuses of CR a minimum of 4 weeks apart documented before progression.
  - Partial Response (PR) (applicable only to patients with measurable disease at baseline): Two objective statuses of PR or better (PR followed by PR or PR followed by CR) a minimum of 4 weeks apart documented before progression, but not qualifying as CR. Sequences of PR- Stable- PR are considered PRs as long as the 2 PR responses are observed at a minimum of 4 weeks apart.
  - Stable Disease (SD) (applicable only to patients with measurable disease at baseline): At least 1 objective status of stable disease or better documented at least 6 weeks after 'start date' and before progression but not qualifying as CR or PR. In this document, 'start date' for a patient is the date of first treatment (if study treatment start date is not available, date of enrollment is used) for non-randomized trials and the date of randomization for randomized trials.
  - Progressive Disease (PD): Progression documented within 17 weeks after 'start date' and not qualifying as CR, PR or SD.
  - Non-CR/non-PD (applicable only to patients with non-measurable disease at baseline): At least 1 non-CR/non-PD assessment (or better) documented at least 6 weeks after 'start date' and before first documentation of progression (and not qualifying for CR or PR).
  - 
  - Not Evaluable (NE): All other cases. Note that reasons for NE should be summarized and the following reasons could be used:
    - No adequate baseline assessment
    - No evidence of disease at baseline
    - No post-baseline assessments due to early death (ie, death prior to 6 weeks after 'start date')
    - No post-baseline assessments due to other reasons
    - All post-baseline assessments have overall response NE

- New anticancer therapy started before first post-baseline assessment
- SD of insufficient duration (< 6 weeks after 'start date' without further evaluable tumor assessments)
- PD too late (> 17 weeks after 'start date')
- Special and rare cases where BOR is NE due to both SD of insufficient duration ('too early') and late PD will be classified as 'SD of insufficient duration'.
- An objective status of PR, SD, or Non-CR/Non-PD cannot follow one of CR. SD can follow PR only in the rare case that tumor increases by less than 20% from the nadir, but enough that a previously documented 30% decrease from baseline no longer holds. If this occurs, the sequence PR-SD-PR is considered a confirmed PR. A sequence of PR – SD – SD – PD would be a best response of SD if the window for SD definition has been met.
- Unconfirmed CR (uCR) is defined as one objective status of CR documented before PD, while confirmed CR requires two objective statuses of CR a minimum of four weeks apart documented before PD. Sequences of CR - Non-evaluable - CR are considered confirmed CR as long as the two CR responses are observed at a minimum of 4 weeks apart. Similarly, unconfirmed PR (uPR) is defined as one objective status of PR documented before PD but not qualifying as uCR. Confirmed PR is defined as two objective statuses of PR or better (PR followed by PR or PR followed by CR) a minimum of four weeks apart documented before PD, but not qualifying as CR. Sequences of PR - Stable Disease or Non-evaluable - PR are considered PRs as long as the two PR responses are observed at a minimum of 4 weeks apart. Based on these definitions, the unconfirmed ORR analysis will include both confirmed CR or PR and unconfirmed CR or PR as responders, whereas the confirmed ORR analysis will only include confirmed CR or PR as responders.

Descriptive statistics (frequency and percentage) and 95% confidence interval will be provided.

2. DOR is defined as the time from first documentation of CR or PR to date of first documentation of PD or death due to any cause. The responders who have not disease progressed at the time of analysis will be censored at the last available tumor scan date. Both confirmed DOR and unconfirmed DOR (uDOR) will be determined separately for the subset of participants with a confirmed and unconfirmed objective response of CR or PR.
3. *CBR is defined as the proportion of patients with a best overall response (BOR) of CR, PR or SD lasting for 24 weeks.*

4. *PFS is defined as the time from start date to date of first documentation of progression as per RECIST 1.1, or death due to any cause. Progression is defined as the appearance of local, regional or distant disease of the same type after complete response or progression of pre-existing lesions. It does not include second primary malignancies of unrelated types.*

PFS will be summarized using the Kaplan-Meier method, as described in [Section 4.3.4](#), and may also be displayed graphically when appropriate.

5. TTP is the time from start date to the date of the first documentation of PD per RECIST 1.1. Start date is the start of treatment.

TTP will be summarized using the Kaplan-Meier method, as described in [Section 4.3.4](#). TTP may also be displayed graphically when appropriate.

6. *OS is defined as the time from start date to date of death due to any cause. Start date is the start of treatment.*

OS will be summarized using the Kaplan-Meier method, as described in [Section 4.3.4](#). OS may also be displayed graphically when appropriate. Participants last known to be alive are censored at date of last contact. The date of last contact will be derived for participants not known to have died at the analysis data cutoff date using the latest complete date (non-imputed) among AE collection date, vital sign date, tumor assessment date, date of follow up anti-cancer therapy etc. This is not an exclusive list of possible dates. Any retrievable last contact date from the clinical database will be used.

Tumor response data in Part 1, Part 2 and across the two Parts may be summarized with descriptive statistics (frequency and percentage) in the following groups by visit and then best overall response across all visits:

- Overall summary for all doses and all tumor types;
- By tumor type regardless of dose;
- By dose regardless of tumor type;
- By dose and tumor type if data permit.

Summary tables of BOR, DOR, PFS, TTP, and OS may be provided by the groups aforementioned when deemed necessary (eg, if there are  $\geq 5$  patients in a specific group).

Efficacy listings (tumor measurements listings and tumor response listings) will be provided that include the investigator provided tumor measurement data, tumor response, BOR, DOR, first CR/PR date, last date with CR or PR, most recent date without progression, progression date, death date, and last tumor assessment date, etc.

Swimmer plot for individual clinical response and time on treatment, waterfall plot for individual tumor size percent change from baseline, and spider plot for individual tumor size percent change from baseline over time will be presented.

